**Primary outcome**					
	**HIV testing**				
		Tested during intervention period^b^	✓^c^	✓	✓
		Interval and frequency of test	✓	✓	✓
		Reason for test [43]	✓	✓	✓
		Perceived benefit of HIV testing	✓	✓	✓
**Secondary outcomes**					
	**Behavioral intentions**				✓
		Intent to test [38]			✓
		Intent to seek PrEP^d^ [41]	✓		✓
		Intent to reduce risky behaviors [44]			✓
	HIV knowledge [39]		✓	✓	✓
	Perceived susceptibility to HIV [40]				✓
	**Risk assessment**				
		Sexual behaviors	✓	✓	✓
		Ever STD^e^ diagnoses	✓	✓	✓
		Alcohol and illicit drug use [45]	✓	✓	✓
	Perceived norms [46]				✓
	**PrEP**				✓
		Knowledge and screening [41,42]	✓		✓
		Use or uptake			✓
	**Self-efficacy or likelihood of action**				
		Ability to negotiate condom use [29]	✓		✓
		Encourage partners or friends or peers to get HIV testing	✓		✓
	**Game and paradata**				
		Game downloads		✓	✓
		Frequency and duration of game play		✓	✓
		Game satisfaction [35]		✓	✓
		Usability [36]		✓	✓
		Teaching approach [37]		✓	✓
		CDC^f^ Risk Estimator scores		✓	✓
		Number of linkages to HIV testing locator		✓	✓
		Number of linkages to PrEP locator		✓	✓
		Recommend app to friend or share on social media		✓	✓
**Modifying factors**					
	Demographics		✓	✓	✓
	Use of social media and gaming		✓	✓	✓
	Exposure to health or sex education programs		✓	✓	✓
	Perceived barriers to HIV testing		✓		✓

^a^RCT: randomized controlled trial.

^b^Verification of HIV testing and pre-exposure prophylaxis uptake will be conducted through photos and in-depth interviews.

^c^The tick mark indicates that the measure will be assessed during that specific phase of the study.

^d^PrEP: pre-exposure prophylaxis.

^e^STD: sexually transmitted disease.

^f^CDC: Centers for Disease Control and Prevention.

### Statistical Analysis

In our pilot study [33], we found that approximately 10% of sexually active AYAs reported being tested for HIV in the past 4-6 months. A sample of approximately 300 subjects (150 per arm) would achieve >80% power to detect a moderate effect corresponding to a difference of at least 13 percentage points (equivalent to a relative risk of 2.3 assuming a 10% prevalence of HIV testing in the past 4-6 months in the control group) in HIV testing between the intervention and control groups after 6 months using a two-sided test at a 5% significance level and assuming a 16% attrition rate after 6 months. All data will be inspected for inaccurate input (eg, out-of-range values, implausible means, and variation). We will first summarize the outcome measures descriptively overall and within each intervention arm at each time point. We will make every effort to obtain all data. Any patterns of missingness will be investigated and reported. Sensitivity analyses, including rerunning analyses with imputed values for missing data, will be conducted to assess the impact of missingness on the study findings.

All primary analyses will be conducted using an intent-to-treat approach. The primary analysis will focus on differences between the treatment and control groups at the 6-month follow-up visit using a chi-square test for independence (the outcome will be taken as having had an affirmative response on the outcome measure during the 6-month study period). We will also investigate the differences between the rates of HIV testing in the treatment and control groups, stratifying by age (13-17 years vs 18-24 years) and sexual orientation (LGBTQ+ vs heterosexual identity). We will perform a longitudinal analysis on the repeated measures from each subject using logistic mixed effects models with a subject-specific random intercept. In each model, we will include time as a 4-level categorical predictor (with baseline serving as the reference level) as well as a treatment indicator and time-by-treatment interaction. We will jointly test the interaction coefficients to determine if the effect of treatment varies over time. If the effect is found to vary over time, we will test the intervention effect at each time point and characterize the difference between the treatment and control groups using risk differences and their corresponding 95% CIs. If no evidence of a time-by-treatment interaction is present, we will refit the logistic model without the interaction terms and provide the overall intervention effect and its corresponding 95% CI.

Furthermore, we will provide a descriptive analysis of each secondary outcome overall and within each intervention arm at each time point. Secondary outcomes will also be compared between the treatment and control groups using one-tailed *t* tests for continuous measures and chi-square tests for categorical measures. The corresponding group differences (in mean scores or proportions) and their 95% CIs will be reported. Within the intervention group, we will investigate game use changes over time and whether there exists a dose-response relationship between various game use indicators (eg, amount of time playing the game) and the various survey responses, including HIV testing, intent to test for HIV, PrEP uptake, and intent to seek PrEP as well as the other secondary outcomes. Qualitative data from IDIs will be transcribed and involve thematic coding using Atlas.ti version 7.0 to identify themes regarding intervention delivery and acceptability.

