### Randomized Controlled Trial

#### Overview

We will evaluate the impact of the life-simulation game compared with app-based HIV educational materials in an RCT with 300 AYAs. To enroll a sample representative of diverse racial or ethnic and sexual behaviors as well as a sample of non–clinic-attending AYAs, recruitment will occur primarily through social media. We will place targeted advertisements toward YMSM and Black and Hispanic AYAs on social media sites, such as Facebook, Instagram, and Snapchat. In addition, we will provide recruitment materials with quick response codes to the DC Health and Montgomery county school-based health programs. Interested AYAs will click on an advertisement and be directed to a web-based eligibility screener to determine their age, gender, sexual behaviors and orientation, state of residence, and availability of a reliable cell phone. The eligibility of the participants will be confirmed by the project staff via phone. Eligible participants will then provide electronic consent and complete the baseline survey electronically. Participants will be randomized using the block randomization method designed to ensure groups of equal sample sizes (1:1). Participants will be randomized in blocks of 6, stratified by age (13-17 years and 18-24 years) and sexual behavior (LGBTQ+ vs heterosexual), using a random number generator for assignment. Randomization will occur through the HIPAA-compliant participant management database platform. We will compare conditions on HIV testing, knowledge, risk behaviors, and PrEP access at enrollment and at 1, 3, and 6 months post enrollment via electronic survey assessments. At 6 months, a subset of intervention participants (n=25) will participate in in-depth *exit* interviews regarding their experience being in the study. A schematic of the study design is shown in Figure 5.

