#### Measures

Electronic surveys via REDCap will be used to assess the behavior at baseline and at 1, 3, and 6 months post enrollment, as it is confidential and allows for complex branching or skip patterns [34]. Participants will be emailed the REDCap surveys 7 days before their designated completion date, on their completion date, and 7 days after their completion date if not completed. Standard items will be administered to gather demographic data (including age, educational level, sexual orientation, socioeconomic status, race, and ethnicity). Surveys will collect information on the following validated domains: HIV- and PrEP-related knowledge; self-reported sexual and HIV risk behaviors; self-perceived risk for HIV; perceived norms; barriers to HIV testing; reported HIV testing and PrEP uptake; behavioral intentions including intent to test for HIV; seeking PrEP; and reducing risky behaviors, self-efficacy, and game use, interest, acceptability, and usability.

At 6 months, a purposely selected subset of intervention participants (n=25) will participate in IDIs regarding their experience being in the study. The IDIs will be conducted by trained qualitative interviewers and will follow semistructured interview guides. The IDIs will assess the extent to which app components facilitate or inhibit HIV testing. Central to the IDIs will be understanding the participants’ use of the app. To obtain a range of perspectives, we will seek feedback from participants stratified by sexual behaviors (heterosexual vs LGBTQ+), age group (13-17 years vs 18-24 years), whether they sought and received HIV testing, and levels of game play and locator use based on the paradata (none, low-moderate, and high use).

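### The primary chi-square test leaves out the randomisation strata and baseline HIV testing; adjusting for them offers a possible efficiency gain, not a correction of bias

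*Protocol article*

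**What the plan says.** The Statistical Analysis section fixes the primary comparison: "The primary analysis will focus on differences between the treatment and control groups at the 6-month follow-up visit using a chi-square test for independence". It names no covariate or stratum for that test.

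The Overview of the Randomized Controlled Trial section describes the allocation: "Participants will be randomized in blocks of 6, stratified by age (13-17 years and 18-24 years) and sexual behavior (LGBTQ+ vs heterosexual"), under a scheme "designed to ensure groups of equal sample sizes (1:1"). It also places the baseline survey before randomisation.

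The Measures section provides the baseline value of the outcome: "Electronic surveys via REDCap will be used to assess the behavior at baseline and at 1, 3, and 6 months post enrollment". The listed survey domains include "reported HIV testing and PrEP uptake".

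Two further analyses in the Statistical Analysis section touch this information:

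- HIV testing rates will also be compared between arms "stratifying by age (13-17 years vs 18-24 years) and sexual orientation (LGBTQ+ vs heterosexual identity").
- A logistic mixed model with a subject-specific random intercept takes baseline as the reference level of time. Its listed terms are time, treatment and their interaction, without the strata.

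Both are additional to the primary test.

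**The concern.** Stratified randomisation balances the arms on the stratification factors. If those factors predict the outcome, an unstratified test still charges their variation to chance, so it rejects too rarely under the null and loses some power under the alternative. The same reasoning applies to a prognostic baseline measure, and earlier HIV testing is a natural candidate for predicting later testing. The article itself suggests that age matters: under Secondary Outcomes it ties the age range and barriers such as parental knowledge to whether young people receive a test.

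What is at stake is precision. The sample size only just delivers 80% power, so any efficiency left unused in the primary test is efficiency the trial could have had from variables it already plans to collect.

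**Working it through.** **Inputs from the Statistical Analysis section.** 150 per arm, 16% attrition, 10% in control, a 13-point difference (so 23% with the game), two-sided 5%.

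**Step 1: reproduce the stated power.**

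Analysed per arm: 150 × 0.84 = 126. Pooled rate: (0.10 + 0.23)/2 = 0.165.

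- Null SE = √(2 × 0.165 × 0.835/126) = 0.04676, and 1.96 × 0.04676 = 0.0917
- Alternative SE = √((0.10 × 0.90 + 0.23 × 0.77)/126) = √(0.2671/126) = 0.04604
- Power = Φ((0.13 − 0.0917)/0.04604) = Φ(0.83) = 79.8%

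Exact binomial enumeration of the uncorrected chi-square gives 80.3%. The stated figure of above 80% is therefore reproduced, but with nothing to spare. 80% power needs 127 per arm, and 127/0.84 = 151.2, so 152 per arm should be recruited against 150 planned. With a continuity correction the exact power is 75.6%.

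**Step 2: bracket the effect of adjustment.** The documents give no prognostic strength, so the following are assumptions: strata split 50/50, 10% tested at baseline unless noted, and overall rates held at 10% versus 23%. Each setting was simulated 5,000 times with four strata, blocks of 6 and random 16% attrition. The chi-square was compared with Cochran-Mantel-Haenszel (CMH) tests.

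| Assumed odds ratios: age / LGBTQ+ / baseline testing | Chi-square | CMH, strata | CMH, strata + baseline | Change, last vs first |
|---|---|---|---|---|
| 1 / 1 / 1 | 81.4% | 81.2% | 80.4% | about −1 |
| 2 / 1.5 / 3 | 81.0% | 81.2% | 81.1% | about 0 |
| 3 / 2 / 3 | 81.4% | 82.7% | 82.4% | about +1 |
| 3 / 2 / 6 | 79.4% | 80.9% | 82.8% | about +3 |
| 3 / 2 / 6, 30% tested at baseline | 81.4% | 82.3% | 85.8% | about +4 |
| 4 / 3 / 10 | 80.6% | 83.1% | 86.2% | about +6 |

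The Monte Carlo standard error of one power estimate is √(0.8 × 0.2/5,000) = 0.6 points. The strata alone are worth about 0 to +3 points. Under the null, rejection was 4.3–5.7% for the chi-square and 4.6–5.9% for the CMH on strata and baseline.

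**Step 3: the same question with logistic regression.** A separate simulation of the adjusted logistic model (252 analysed, 3,000 runs per setting) gave gains of about 0 points with no prognostic value, 2 with weak and 4–5 with strong factors. Type I error was about 5–6% for both tests. This agrees with the table.

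**Step 4: is the model small enough?** Expected events at the design rates: 126 × 0.10 + 126 × 0.23 = 12.6 + 29.0 = 41.6. With four terms (arm, age, LGBTQ+, baseline testing) that is 41.6/4, about 10 events per term. If both arms stay at 10% there are about 25 events, or about 6 per term. That is thin but workable, and the null simulations show no material inflation.

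**Step 5: the labels side by side.** The Overview has "stratified by age (13-17 years and 18-24 years) and sexual behavior (LGBTQ+ vs heterosexual"). The Statistical Analysis section has "stratifying by age (13-17 years vs 18-24 years) and sexual orientation (LGBTQ+ vs heterosexual identity"). The categories are the same, but the variable is named once as behaviour and once as orientation or identity.

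**The case against.** The strongest reply is that nothing here is an error. A chi-square after stratified randomisation is valid and, if anything, conservative. The power statement is made for essentially this test and reproduces. All of that stands.

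A second reply is that the gain is assumed, not shown. That also stands: with weak prognosis it is nil, and with none the finely stratified CMH test gives up about a point. Simulations restricted to strong odds ratios (4–10 for baseline testing) would show gains of about 3 to 6 points only because weaker settings were left out.

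Third, the plan already uses baseline testing in the mixed model and the strata in the additional rates. True, and it deserves credit, but neither supplies the primary p-value and the mixed model lists no strata.

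A reader might also infer two stronger points that the article does not support. One is that the lack of a treatment-by-stratum interaction test will lead to false subgroup claims. The article announces no such claims, and an analysis plan commonly supplies that test. The other is that the groups analysed will differ from those randomised. The article uses behaviour and orientation loosely for the same two categories, so what is shown is a naming inconsistency.

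**Conclusion.** The point holds as an efficiency weakness. The primary test, as fixed, uses neither the stratification factors nor the baseline value of the outcome, in a design with about 80% power and no reserve. Adjustment is worth between about −1 and +6 points of power, with type I error near 5%. Where the trial falls in that range depends on prognostic strengths that the documents do not give.

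It would be tempting to conclude that the chi-square biases the result or certainly wastes power. Neither follows: the test is valid, and the loss may be close to zero. The case for changing it is that the likely downside is about a point at most, the possible upside is several points, and no further data collection is needed.

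**What to change.** In the Statistical Analysis section, replace the primary chi-square with a logistic regression on arm, age stratum, LGBTQ+ stratum as randomised, and baseline self-reported HIV testing in the past 6 months (yes/no).

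- Take the primary p-value from the arm term.
- Report the standardised risk difference with 95% CI: the average, over all analysed participants, of the predicted risk with the game minus the predicted risk with the control app. This keeps the result on the scale of the 13-point target.
- Keep the unadjusted chi-square as a supporting analysis.
- Name the LGBTQ+ versus heterosexual variable once, and use the randomised version in both the Overview and the Statistical Analysis section.

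The cost is wording. The strata exist at randomisation and testing is already a baseline survey domain. The article does not state the look-back of the baseline item, so confirm that it covers 6 months, as the outcome does. The Results section places the project at its formative phase, so the change can be made before any trial data exist.

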#### Intervention Delivery

Intervention participants will have access to the full revised study game for 3 months from the time of enrollment and will be able to play the game and have up to 30 hours of content available. To sustain interest and engagement over the study period and maximize potential efficacy, new downloadable game content will be available every 4 weeks post enrollment through the 3-month follow-up.

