### Outcomes

#### Primary Outcomes

The primary outcome measure for the study is HIV testing. This will be measured as self-reported HIV testing in the past 6 months. For all participants who report testing, we will attempt to validate reported testing by eliciting a description of the HIV testing process and requesting that a secure photo of their test results be sent to study staff to minimize social desirability bias. We will compare self-reported HIV testing between the 2 groups at 6 months.

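### With a 6-month recall at months 1, 3 and 6, the longitudinal HIV-testing model mixes how much of the window follows randomisation with any real change in effect over time

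*Protocol article*

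**What the plan says.** Under Primary Outcomes the protocol article defines HIV testing thus: "This will be measured as self-reported HIV testing in the past 6 months". No other recall length is given for this outcome.

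The measure is collected repeatedly. The Measures section says "Electronic surveys via REDCap will be used to assess the behavior at baseline and at 1, 3, and 6 months post enrollment", and the RCT Overview says "We will compare conditions on HIV testing, knowledge, risk behaviors, and PrEP access at enrollment and at 1, 3, and 6 months post enrollment".

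Statistical Analysis puts these responses into one model: "We will perform a longitudinal analysis on the repeated measures from each subject using logistic mixed effects models with a subject-specific random intercept". Time has four levels with baseline as reference, plus treatment and their interaction. The interaction is given a definite meaning: "We will jointly test the interaction coefficients to determine if the effect of treatment varies over time". What follows depends on it: "If the effect is found to vary over time, we will test the intervention effect at each time point", with risk differences and confidence intervals. Otherwise a single overall effect is reported.

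Two other statements matter. Intervention Delivery limits exposure: "Intervention participants will have access to the full revised study game for 3 months from the time of enrollment". Table 1 lists, among the HIV-testing items for the RCT, "Interval and frequency of test".

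**The concern.** A 6-month look-back asked 1 month after enrolment mostly describes the time before enrolment. At month 3 it is half and half, and only at month 6 does it describe study time alone. The windows also overlap one another. The month-specific arm contrasts therefore differ in how much of the outcome the intervention could have influenced, whatever the effect is doing.

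The plan reads differences among those contrasts as the effect varying over time. Two readings are at risk. A constant effect can look as if it builds slowly. An effect that ends with access can look the same at month 6 as at month 3, because the month-6 window still contains months 0 to 3. Access stops at month 3 and follow-up continues to month 6, so onset and durability are what this analysis could add to the single month-6 test.

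**Working it through.** **Inputs from the document.** Recall 6 months (Primary Outcomes); surveys at months 0, 1, 3 and 6 (Measures); access for 3 months (Intervention Delivery); control 10%, difference 13 points, 150 per arm, 16% attrition, two-sided 5% (Statistical Analysis).

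**Assumptions.** The 10% applies to a 6-month window (the source figure is given for 4-6 months). Testing rates are constant within periods and equal in both arms before enrolment. Tests in separate periods are independent. There are 150 × 0.84 = 126 analysed per arm at every visit.

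**The plan's own figure.** A two-proportion test of 10% versus 23% with 126 per arm has power 79.8%. The stated power of just over 80% is reproduced to rounding.

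**Share of the window after randomisation**, which needs no rate assumption: 1/6 = 17%, 3/6 = 50%, 6/6 = 100%.

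**Monthly rates.** Control: −ln(0.90)/6 = 0.01756. Intervention: −ln(0.77)/6 = 0.04356. Ratio 2.48. The probability of a reported test at month v is 1 − exp(−cumulative rate from v − 6 to v), using the control rate before enrolment.

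**Case A, constant rate ratio 2.48 from enrolment.**

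| Visit | Cumulative rate, intervention | Intervention | Control | Risk difference | Odds ratio | Power |
|---|---|---|---|---|---|---|
| 1 | 5 × 0.01756 + 1 × 0.04356 = 0.1314 | 12.3% | 10% | 2.3 | 1.26 | 8% |
| 3 | 3 × 0.01756 + 3 × 0.04356 = 0.1834 | 16.8% | 10% | 6.8 | 1.81 | 35% |
| 6 | 6 × 0.04356 = 0.2614 | 23.0% | 10% | 13.0 | 2.69 | 80% |

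**Case B, effect only in months 0-3, sized to reach 23% at month 6.** The access-period rate is (0.2614 − 3 × 0.01756)/3 = 0.06956, a ratio of 3.96, falling to 1.00 after month 3.

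| Visit | Cumulative rate, intervention | Intervention | Risk difference | Odds ratio |
|---|---|---|---|---|
| 1 | 5 × 0.01756 + 0.06956 = 0.1574 | 14.6% | 4.6 | 1.53 |
| 3 | 3 × 0.01756 + 3 × 0.06956 = 0.2614 | 23.0% | 13.0 | 2.69 |
| 6 | 3 × 0.06956 + 3 × 0.01756 = 0.2614 | 23.0% | 13.0 | 2.69 |

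**Simulated tests** (126 per arm, marginal log odds ratios standing in for the mixed model). The 2-df test asks whether the month-1, month-3 and month-6 odds ratios are equal. It rejects in about 5% of trials with no effect and about 26% in case A, where the rate ratio never changes. In case B, a month-6 versus month-3 contrast rejects in about 5%, the nominal level.

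**Same truths, non-overlapping intervals (0-1, 1-3, 3-6 months).** Case A gives odds ratios 2.51, 2.55 and 2.58. Case B gives 4.07, 4.18 and 1.00. The constant effect now looks constant and the stop is visible.

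**The case against.** The best reply is that the recall at months 1 and 3 is not spelled out. Table 1 labels the outcome as testing within the intervention period, and the chi-square rule refers to the 6-month study period. If follow-up surveys asked about testing since enrolment, the 17/50/100% shares would not apply, and a constant effect would give nearly constant odds ratios (2.51, 2.58, 2.69). This stands as a limit: the point rests on an inference. But 6 months is the only recall the document states, and a post-enrolment label cannot supply the baseline level the model requires. Even under since-enrolment wording, case B would show 13.7 points at month 3 and 13.0 at month 6, so persistence would remain unreadable.

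A reader might infer that the interaction test follows the recall window instead of the effect. That goes too far. With no effect the test holds its 5% level, because pre-enrolment testing is balanced by randomisation. The window dilutes early contrasts and creates no false treatment effect.

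A reader might also cite the planned 3-df test, which rejects in about 28% to 30% of trials in case A. That figure does not isolate the window, because baseline is the reference and any post-randomisation effect contributes to rejection. The 2-df figure is the relevant one.

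Finally, a reader might infer that the trial would report persistence that is not there. The document names no persistence objective and no month-6 versus month-3 contrast. What stands is narrower: similar results at months 3 and 6 could not support such a reading.

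**Conclusion.** The point holds for the longitudinal analysis. The stated measure, used at months 1 and 3, cannot support the stated interpretation of the interaction. Under the plan's 10% versus 23% and constant rates, an unchanging rate ratio of 2.48 appears as 2.3, 6.8 and 13.0 points and is called time-varying in about 26% of trials by the post-baseline test. An effect that ends at month 3 gives an identical 13.0 points at months 3 and 6.

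The window shares follow from the document once the 6-month recall is taken to apply at every survey. The rates, independence and marginal approximation are assumptions. A reader might extend the criticism to the primary result, but the month-6 answer has a window wholly after randomisation, so that comparison is unaffected by this point. This is a change worth making to a supporting analysis.

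**What to change.** In the longitudinal analysis, define HIV testing at months 1, 3 and 6 as a test since the previous survey (0-1, 1-3 and 3-6 months), derived from the test-timing item already listed in Table 1. Use the baseline past-6-month answer as a covariate and not as a level of time. Report interval-specific odds or rate ratios that account for interval length. A complementary log-log model with a log-length offset is one option. Keep the month-6 past-6-month comparison as primary.

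This needs no extra visits or participants, only survey-item or analysis wording. If the timing item does not place a test within an interval, one question on the date of the test is needed.

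The main cost is precision. Expected control events are 126 × 0.0174 = 2.2, 126 × 0.0345 = 4.3 and 126 × 0.0513 = 6.5 per interval. A months 0-3 versus 3-6 contrast has only about 45% to 49% power even if the rate ratio falls from about 4 to 1, and about 22% if it falls from 2.48 to 1. These estimates should be labelled supportive. Recalled test dates will also carry some error.

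### When the interaction test is non-significant, the supportive longitudinal model pools the pre-exposure baseline into its overall effect and shrinks the log odds ratio to about 80% of its true value

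*Protocol article*

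**What the plan says.** All references are to the protocol article.

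- **Primary analysis** (Statistical Analysis): "The primary analysis will focus on differences between the treatment and control groups at the 6-month follow-up visit using a chi-square test for independence".
- **Longitudinal analysis** (same section), in addition to the primary: "logistic mixed effects models with a subject-specific random intercept", in which "we will include time as a 4-level categorical predictor (with baseline serving as the reference level) as well as a treatment indicator and time-by-treatment interaction". Assessments are "at enrollment and at 1, 3, and 6 months post enrollment via electronic survey assessments" (Overview of the randomized trial), so the four levels are baseline, 1, 3 and 6 months, and baseline is a row of the outcome.
- **Gate:** "We will jointly test the interaction coefficients to determine if the effect of treatment varies over time".
- **Branch A, interaction found:** "If the effect is found to vary over time, we will test the intervention effect at each time point", reported as risk differences with 95% CIs.
- **Branch B, no evidence of interaction:** "we will refit the logistic model without the interaction terms and provide the overall intervention effect", with its 95% CI.

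The section does not constrain the arms to be equal at baseline, does not leave baseline out of the overall effect, and states no error control across the two branches.

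**The concern.** The gate is read as a test of whether the effect is constant over time. With baseline as the reference level it is something else: the interaction coefficients are the differences between arms in change from baseline, which is to say they are the intervention effect. The Overview places the baseline survey ahead of randomization, and Intervention Delivery and Control Condition give access for 3 months afterwards, so the expected arm difference at baseline is zero. A non-significant gate therefore does not show a constant effect. It shows only that the test did not detect the arms diverging after baseline.

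Branch B then drops exactly those terms and fits one treatment coefficient across all four occasions. What would be published as the overall effect of the game, with a confidence interval, is a blend of the follow-up effect with a known zero and with any chance imbalance at baseline. A second consequence is that an effect can be claimed through either branch, each at its own 5% level.

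**Working it through.** **Inputs from the document (Statistical Analysis).** 150 per arm, 10% control rate, 13-point difference (so 23%, a ratio of 2.3), two-sided 5%, 16% attrition after 6 months.

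**Inputs assumed.** Gate at 5%; random-intercept SD 1 or 2; 10% at baseline and at every control visit; data missing completely at random.

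**1. The plan's own figure.** 150 × 0.84 = 126 analysed per arm. With pooled p = 0.165, z = (0.13·√126 − 1.96·√(2·0.165·0.835)) / √(0.10·0.90 + 0.23·0.77) = (1.459 − 1.029)/0.517 = 0.83, giving 79.8% power. Exact enumeration of the uncorrected chi-square gives 80.3%. The stated power of more than 80% is reproduced. It belongs to the primary test and is not in question.

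**2. What the refit estimates.** The full model is logit P = b + α_t + δ + γ_t, where b is the subject's intercept, δ + γ_t applies to the game arm only, and γ is zero at baseline. Randomization makes δ = 0 in expectation, so the effect at follow-up t is γ_t. Setting every γ_t = 0 forces one δ to fit one zero contrast and three non-zero ones. With equal weights, a constant effect θ gives δ = (0 + 3θ)/4 = 0.75θ.

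**3. Hand check with information weights** (ignoring within-subject correlation). Per subject per arm, the information on the log odds ratio is:
- baseline: 1/(1/0.09 + 1/0.09) = 0.0450
- each follow-up: 1/(1/0.09 + 1/0.1771) = 0.0597

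The follow-up share is 3·0.0597/(3·0.0597 + 0.0450) = 0.80. Counting the 6-month visit at 0.84, it is 0.79.

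**4. Simulation of the planned rule.** 300 subjects, four visits, 16% missing at 6 months, maximum-likelihood random-intercept fits, 3-df likelihood-ratio gate; 450 runs per alternative and 1,200 under the null.

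| Scenario | SD | True log OR | Median main effect | Ratio | Gate significant | Main-effect power |
|---|---|---|---|---|---|---|
| Constant 23% vs 10% | 1 | 1.12 | 0.90 | 0.80 | 52% | 98% |
| Constant 23% vs 10% | 2 | 1.46 | 1.17 | 0.80 | 63% | 94% |
| Rising 14/19/23% vs 10% | 1 | 1.12 at 6 months | 0.63 | 0.56 | 43% | 77% |
| Rising 14/19/23% vs 10% | 2 | 1.46 at 6 months | 0.80 | 0.55 | 52% | 63% |

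In the rising rows the ratio is to the 6-month value. Against the mean follow-up effect it is 0.79 and 0.77. A simulation with 126 per arm throughout (1,000 runs) gave 0.82 at both SDs for the constant effect. A further 500 runs gave 0.89 vs 1.12 and 1.17 vs 1.46. As odds ratios, the constant case reads about 2.5 instead of 3.1 (SD 1), or 3.2 instead of 4.3 (SD 2).

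**5. How often branch B is reached (constant design effect).** The gate was significant in 52% to 63% of runs in the main set, 47% to 57% with 126 per arm, and 48% to 61% in the 500-run set. Branch B is the complement: about 37% to 53% overall.

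**6. Null error, reading the CIs as tests.**
- Main set: 7.3% to 7.4% counting follow-up time points only, and 8.3% to 8.7% counting all four (simulation error about 0.8 points).
- 126 per arm: 7.8% to 8.3%, and 9.0% to 10.3%.
- 500-run set: about 9% to 11%, with simulation error √(0.1·0.9/500) = 1.3 points.
- Reference: two independent 5% tests give 1 − 0.95² = 9.75%. A single prespecified 6-month contrast in the same model gave 4.6% to 5.3%.

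**The case against.** The strongest reply is that this is not the primary analysis. The 6-month chi-square test stands apart, the sample size rests on it, and the dilution runs toward the null. The article also promises outcome summaries by arm at each time point, so a diluted estimate would not stand alone. All of that holds, and it limits the severity. It does not make the pooled estimate right.

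Several stronger readings are tempting, and the document does not support them:

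- **That keeping baseline as an outcome is itself an error.** It is sound if the arms are constrained equal there. The fault is the unconstrained main effect after the refit.
- **That the refit generally loses the signal.** Under the constant design effect its test keeps 94% to 99% power. Power falls with a rising effect (63% to 77% above), but the article does not assume that pattern.
- **That the false-positive rate doubles.** Branch B promises an estimate and a CI, not a test. The inflation appears only if the CI is read as one, and it is then roughly 7% to 10%.
- **That the plan tests for an effect at baseline.** The wording on time points could include baseline, but no intervention effect exists before exposure, so follow-up only is the fairer reading.
- **That the two branches report incompatible scales.** The article gives no scale for the overall effect, and an unseen analysis plan may set it. Log odds ratios are used here only because the model is logistic.

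**Conclusion.** The point holds for the supportive longitudinal analysis and goes no further. A reader might infer that the trial's main conclusion is at risk. It is not: the primary test and its stated power are untouched.

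The direction of the fault follows from the stated coding alone. Its size rests on the assumed random-intercept SD of 1 to 2, a 5% gate, a 10% rate at baseline and in controls throughout, and ignorable missingness. On those terms, a constant 10% vs 23% effect is reported at about 80% of its true log odds ratio whenever branch B is taken, which is in roughly two trials in five to just over half. If the effect builds up to 23% by 6 months, the pooled figure is about 55% of the 6-month log odds ratio. A build-up is plausible if the 6-month recall window named under Primary Outcomes is also used at the 1-month survey, since most of that window precedes enrollment. The harm is mainly to the estimate; the error inflation is moderate. The rule should be fixed before analysis.

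**What to change.** 1. Keep baseline as an outcome but constrain the arms equal there: time at four levels plus treatment-by-time terms at 1, 3 and 6 months only, with no treatment main effect. Alternatively, model the three follow-ups with baseline testing as a covariate.
2. Name one test in advance: either a single contrast, such as 6 months, or the joint 3-df test of the follow-up terms.
3. Always report the 1-, 3- and 6-month risk differences with 95% CIs, whatever that test shows.
4. Delete the branching on the interaction test. If one summary effect is wanted, define it as an average over the three follow-up visits only.
5. State that this analysis supports the primary 6-month chi-square test.

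The cost is analysis wording and a few lines of code. No new data are needed, and neither the sample size nor the primary analysis changes. With 126 per arm and 1,000 runs, the constrained model had a null error of 4.3% to 5.2%.
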